### Sample size and recruitment

This study is being conducted as part of a PhD thesis. Twelve patients will be recruited over a 12 months period. Previous feasibility work shows this recruitment rate is achievable. Patients will be identified at a weekly neuro-oncology multi-disciplinary team (MDT) meeting; with documentation within MDT case sheet deemed an appropriate referral. Patients will be approached for recruitment after surgery and histological diagnosis of GB. Recruitment will take place for 12 months from the date of opening. Patients referred for the KEATING trial will be offered a screening appointment. A screening log will be maintained for all patients referred to the trial and reasons for ineligibility will be noted.

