### Allocation strategy

Patients will be randomised into MKD or MCT KD groups. The patients will be informed of diet group by telephone. A permuted block randomisation method will be adopted, at a 1:1 ratio using ‘sealedenvelope’™ randomisation system. This will be set up and administered by the statistician ([name]) who is not involved with the recruiting of patients.

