### Intervention design

All participants will be invited to attend clinical consultations pre-diet, on initiating diet, 6 weeks from initiation, 12 weeks from initiation (primary completion) and every 3 months for a total of 12 months (secondary completion) or until dietary discontinuation if prior to this. Telephone consultations will take place post initiation at weeks 1, 3 and 9 to enable dietary ‘fine tuning’ (Table 1 and Fig. 1). All consultations will be undertaken with the same research dietitian. It is not possible to blind the participants or the investigators due to differences between the diets and dietary education required.

**Table 1 Tab1:** Study schedule

	Study period										
		Enrolment/diet allocation	Post allocation (on diet)								Close out
Timeline		1 week post-histology	1 week after clinic 1	1 weeks after clinic 2	3 weeks after clinic 2	6 weeks after clinic 2	9 weeks after clinic 2	12 weeks after clinic 2	6 months after clinic 2	9 months after clinic 2	12 months after clinic 2
Visit window	Post-histology	± 5 days	± 5 days before radiotherapy	± 3 days	± 3 days	± 5 days	± 3 days	± 5 days	± 10 days	± 10 days	± 10 days
Clinic visit	Telephone discussion	Clinic appointment 1 Consent, register, baseline assessment, randomisation	Clinic appointment 2 Commence diet	Telephone review 1	Telephone review 2	Clinic appointment 3 Diet review	Telephone review 3	Clinic appointment 4 Diet review	Clinic appointment 5 Diet review	Clinic appointment 6 Diet review	Clinic appointment 7 Diet review End of trial
Information sheet	X										
Informed consent		X									
Eligibility screen		X									
Randomisation		X									
Medical history review		X									
Medications review		X									
Anthropometry		X				X		X	X	X	X
Biochemistry		X						X	X	X	X
Food diary		X				X		X	X	X	X
Ketone diary						X		X	X	X	X
Quality of life (QoL) questionnaire EORCT QLQ C30		X				X		X	X	X	X
QoL questionnaire QLQ BN20		X				X		X	X	X	X
Food Acceptability Questionnaire		X				X		X	X	X	X
Dietary review		X	X	X	X	X	X	X	X	X	X
Ketone review				X	X	X	X	X	X	X	X

X = procedure carried out

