Dietetic time required for the interventionsDietetic time spent on both clinical and non-clinical activities related to the trial will be recorded to aid future protocol design.
Protocol refinements requiredDeviations from the protocol will be documented on the deviation log. This will be used to refine future protocols and inform future clinical trials.
 Sample size estimates for future trialsData synthesised from this pilot will inform sample size calculations for future phase III clinical trials based on the primary outcome measure of retention.
 Completeness of data for all trial outcomesCompleteness of documented data will be assessed to inform feasibility of future clinical trials.
 Quality of lifeQuality of life will be evaluated though the generic EORTC QLQ C30 and brain cancer-specific QLQ BN 20 validated questionnaires prior to commencing the diet, at week 6, week 12 and every 3 months thereafter or at point of dietary discontinuation if prior to this.
 Food acceptabilityFood acceptability will be assessed through the non-validated Food Acceptability Questionnaire [30] completed prior to commencing the diet, at week 6, week 12 and every 3 months thereafter or at point of dietary discontinuation if prior to this.
 Gastrointestinal side effectsGastrointestinal side effects will be quantified from the EORCT QLQ C30 questionnaire and through informal clinic assessments. The Common Terminology Criteria for Adverse Events ([CTCAE], version 4.0) will be used to grade gastrointestinal side effects.
 Changes to biochemical markersBiochemical markers (fasting lipid, fasting glucose, liver, renal and bone profiles) will be undertaken at baseline and repeated every 3 months until discontinuation of diet.
 Anthropometric changesAnthropometry (height, weight, body mass index (BMI), waist circumference, mid-upper arm circumference (MUAC), mid-arm muscle circumference (MAMC), tricep skinfold (TSF), hand grip strength (HGS) and fat mass) will be measured at baseline, week 6, week 12 and every 3 months thereafter. All measurements will be undertaken as per measurement methodology cited in Parenteral and Enteral Nutrition Group (PENG), pocket guide to clinical nutrition [29].

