### Withdrawal

If there is a change in the patient’s condition that in the clinician’s opinion justifies dietary discontinuation or if the patient withdraws consent, the patient will be withdrawn from dietary treatment. In this case, data up until the point of withdrawal will be used in analysis. Unless the patient specifically withdraws consent further data will be gathered for progression-free survival and overall survival analysis.

Patients will be made aware at the point of consent that they can withdraw at any time. No reason will be required. Should a patient withdraw, data will be included in the analysis until the point of withdrawal, unless the patient states otherwise. If they wish for their data to be excluded entirely, a CRF for destruction of data will be completed.

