### Statistical considerations

#### Sample size

Feasibility data demonstrates a likely retention rate of 70% participants at 12 weeks. With a sample size of 12, we will be able to estimate retention rates of 70% to within a 95% confidence interval of ± 25.93% (Hooper [36]). Billingham et al. [37] demonstrate a median sample size of 30 (range 8–114 participants) for UK pilot studies, whilst Hertzog [38] reports on the statistical adequacy for sample sizes of 10–40, thus further justifying a sample size of 12 for the current trial.

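### Quality-of-life forms end when the diet ends, so the week-6 and week-12 summaries by diet describe only patients still on diet and do not compare the randomised groups

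*Protocol article*

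**What the plan says.** Three sections of the protocol article set the rule, and they agree.

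- **Secondary outcome measures, quality of life:** the plan takes the QLQ-C30 and QLQ-BN20 "questionnaires prior to commencing the diet, at week 6, week 12 and every 3 months thereafter or at point of dietary discontinuation if prior".
- **Intervention design:** consultations are offered at fixed points up to week 12 and then "every 3 months for a total of 12 months (secondary completion) or until dietary discontinuation if prior to this".
- **Withdrawal:** for a patient taken off the diet, "data up until the point of withdrawal will be used in analysis". Unless consent is withdrawn, "further data will be gathered for progression-free survival and overall survival analysis". Quality of life is not named among the data that continue.

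The Abstract gives the impact of the two diets on quality of life as part of the aim, and the Aims and objectives list it under patient impact. The Analysis plan summarises it descriptively.

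**The concern.** Whether a week-12 form exists depends on something that happens after randomisation, namely staying on the diet. The Withdrawal section names a change in the patient's condition as one ground for stopping, so patients without a week-12 form may well differ from those with one. The form at stopping falls at a different time for each patient and does not give a week-6 or week-12 value.

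A week-12 summary by diet then describes two selected subgroups, and randomisation no longer makes them comparable. The pilot would also show nothing about whether quality of life can be collected after a patient stops the diet, which the later trial would want to know. A later analysis plan can decide how to use the stopping forms, but it cannot recover forms that were never collected.

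**Working it through.** **Inputs from the protocol article**
- Sample size: "Twelve patients will be recruited over a 12 months period" (Sample size and recruitment).
- Allocation: "A permuted block randomisation method will be adopted, at a 1:1 ratio" (Allocation strategy), so about 6 per diet.
- Retention: "Feasibility data demonstrates a likely retention rate of 70% participants at 12 weeks" (Sample size), so a drop-out share d = 0.30.

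**The plan's own figure.** The half-width of the 95% confidence interval for 70% retention with 12 patients is 1.96 × √(0.70 × 0.30 / 12) = 0.2593, which reproduces the stated ±25.93%. No figure in the plan is in dispute.

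**Expected week-12 forms.** This takes everyone not retained as off diet by week 12.
- With a form: 0.70 × 12 = 8.4 patients, or 0.70 × 6 = 4.2 per diet.
- Without a form: 0.30 × 12 = 3.6 patients, or 0.30 × 6 = 1.8 per diet.

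**Chance that a diet of 6 lacks week-12 forms** (binomial, patients independent)
- At least one missing at 70% retention: 1 − 0.7⁶ = 0.88.
- At least two missing at 70% retention: 1 − 0.7⁶ − 6 × 0.3 × 0.7⁵ = 1 − 0.118 − 0.303 = 0.58.
- At least one missing at 50% retention: 1 − 0.5⁶ = 0.98. At 90% retention: 1 − 0.9⁶ = 0.47.

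**Size of the shift.** Let g be the week-12 mean of patients on diet minus the week-12 mean of patients who stopped. The all-randomised mean is (1 − d) × on-diet mean + d × off-diet mean, so

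on-diet mean − all-randomised mean = d × g.

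The document gives no value for g. The values below are assumptions on a 0–100 scale.

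| Assumed g | Shift at d = 0.30 |
|---|---|
| −10 (stoppers recover and score higher) | −3 |
| 0 | 0 |
| 10 | 3 |
| 20 | 6 |

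**Between diets, as an illustration.** Suppose 3 of 6 stay on one diet and 5 of 6 on the other, with equal on-diet means and the same g in both. The on-diet summaries then agree, while the all-randomised means differ by (3/6 − 1/6) × g. That is 3.3 points for g = 10, 6.7 points for g = 20, none for g = 0, and 3.3 points the other way for g = −10.

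**The case against.** A reader might infer that a diet which drives patients away could pass as the equal of one that does not. The protocol does not support that. Retention is the primary outcome, counted over all randomised patients with reasons and time to discontinuation, and the Defining success section grades it separately for each diet. In the illustration above, 3 of 6 (50%) is amber and 5 of 6 (83%) is green. The level of quality of life is not a progression criterion. This objection stands and limits the point to the quality-of-life description.

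A reader might also infer that the bias always flatters the worse-tolerated diet. That needs stoppers to score lower at week 12, and the document gives no evidence either way. If a diet lowers quality of life and stopping relieves it, the gap could vanish or reverse. This also stands.

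The form at stopping does capture something, and the analysis plan, which is not shown, could build a last-on-diet summary from it. That would be a legitimate summary, but of a different quantity: it is not quality of life at a common time by randomised diet.

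The shift is also small against chance variation. With an assumed standard deviation of 15 to 25 points, the standard error of a difference between 6 and 6 patients is 15 × √(1/6 + 1/6) = 8.7 to 25 × √(1/6 + 1/6) = 14.4 points. The article plans descriptive statistics and promises caution. This is a reason to rank the point low. It does not justify leaving out forms that are cheap to collect.

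Finally, one might assume that stoppers remain in contact because survival data continue. The document says that those data will be gathered, but not how. They might come from routine records, so the ease of reaching these patients is not established.

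**Conclusion.** The point holds as a cheap improvement to data collection. After one off-schedule form at discontinuation no further EORTC forms are planned, so scheduled-visit summaries by diet cover only patients still on diet. This follows from the text and needs no assumption about scores.

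At 70% retention, about 4 of 12 patients would have no week-12 value. The resulting shift of 3 to 6 points rests on an assumed gap of 10 to 20 points in favour of stayers, and its sign is not known. The consequence is confined to the descriptive quality-of-life comparison and its use in planning the later trial. It does not reach the choice of diet on retention.

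**What to change.** Collect the QLQ-C30 and QLQ-BN20 at weeks 6 and 12, by post or telephone, from every randomised patient who has not withdrawn consent, whether or not on diet. Keep the form at stopping as an addition. Report quality of life by randomised diet for all patients beside the on-diet summary, with the number contributing per diet at each time.

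Three places need matching wording: the quality-of-life outcome, the Intervention design (follow-up for questionnaires separate from diet visits), and the Withdrawal section, which should distinguish stopping the diet from withdrawing consent to data collection and let the later forms enter the analysis.

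The cost is at most two questionnaire sets for each patient who stops early. With 3.6 such patients expected, that is at most 2 × 3.6 = 7.2, or about 7 sets in all. There is a small patient burden, possible non-response from patients whose condition has worsened (to be reported with reasons), and a change to the information sheet.

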### Adverse events

The main health risks associated with the diet include gastrointestinal intolerance (such as diarrhoea, constipation, nausea, reflux, abdominal discomfort), altered or raised cholesterol, kidney stones and decreased bone density [44].

To monitor these health risks biochemistry will be monitored every 3 months (renal, bone, LFT, fasting cholesterol and glucose). Gastrointestinal side effects will be assessed using the Common Terminology Criteria for Adverse Events (CTCAE, version 4, [45]), and dietary adjustments will be made to aid symptom relief when possible.

All adverse events (AE) will be reported. The National Institute of Health Research (NIHR) ‘decision tree for adverse event reporting’ [46] will be used to grade AE and serious adverse events (SAE) severity.

An AE or SAE will be reported by the investigator; however the chief investigator will be responsible for determining causality. The trial would close early should SAEs occur as a direct result of the trial intervention.

Trigger monitoring will be adopted which will be managed by the University of Liverpool (the Sponsor).

All SAE will be reported to the Trial Steering Committee within 1 week of the event.

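### For patients who stay on diet, no structured gastrointestinal assessment is scheduled before week 6, and the contacts at which symptoms are elicited for CTCAE grading are not named

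*Protocol article*

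**What the plan says.** The Secondary outcome measures section says that gastrointestinal side effects "will be quantified from the EORCT QLQ C30 questionnaire and through informal clinic assessments". The next sentence adds that CTCAE version 4.0 "will be used to grade gastrointestinal side effects". The same section schedules the QLQ-C30 "prior to commencing the diet, at week 6, week 12 and every 3 months thereafter or at point of dietary discontinuation if prior to this", and the questionnaire row of Table 1 agrees for the scheduled visits.

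The Intervention design section places clinic consultations "pre-diet, on initiating diet, 6 weeks from initiation, 12 weeks from initiation (primary completion") and then every 3 months. Between them, "Telephone consultations will take place post initiation at weeks 1, 3 and 9 to enable dietary ‘fine tuning". At those calls Table 1 marks dietary review and ketone review and nothing else. It has no row for gastrointestinal symptoms, CTCAE grades or adverse events at any contact.

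The Adverse events section states: "The main health risks associated with the diet include gastrointestinal intolerance (such as diarrhoea, constipation, nausea, reflux, abdominal discomfort"). It goes on to say that "dietary adjustments will be made to aid symptom relief when possible", and that every adverse event is to be reported, with no limit in time. Habitual gastrointestinal complaints are recorded at baseline (Baseline data collection).

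**The concern.** Tolerability is a stated aim, and the pilot is meant to show which of two diets is more deliverable. The diets differ in the amount and type of fat, and one uses a medium chain supplement (Dietary intervention). The weeks just after initiation are when the dietitian fine-tunes the diet, and the article foresees changes to relieve symptoms. The sources named for this outcome reach those weeks weakly: one is a questionnaire first due on diet at week 6, and the other is an informal assessment at clinic, with no clinic between initiation and week 6.

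Two things are at stake. The gastrointestinal burden of each diet could be under-recorded among patients who continue after an adjustment. The shortfall could also differ between the diets, because the same unblinded dietitian conducts all consultations and no standard question is stated. A smaller consequence concerns the Defining success section, which asks for 75% of proposed data collection for each end point, by diet. An informal assessment with no stated occasions gives no denominator for its part of this end point.

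**Working it through.** The plan gives no figure for this outcome. Its one computed figure, the precision of the retention rate, reproduces as 1.96 × √(0.7 × 0.3 / 12) = 0.2593, the stated ± 25.93%. It plays no part here. The check is a count of scheduled contacts.

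**Inputs.** Contacts, windows and procedures come from Table 1 (Intervention design), questionnaire timing from Secondary outcome measures.

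| Contact after initiation | Day | Mode | QLQ-C30 | Ketone review |
|---|---|---|---|---|
| Week 1 | 7 | telephone | no | yes |
| Week 3 | 21 | telephone | no | yes |
| Week 6 | 42 | clinic | yes | yes |
| Week 9 | 63 | telephone | no | yes |
| Week 12 | 84 | clinic | yes | yes |

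**Step 1: coverage.** The questionnaire is scheduled at 2 of 5 contacts to week 12, and at 0 of the 2 contacts before week 6. Ketone review is scheduled at 5 of 5.

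**Step 2: first on-diet measurement, for a patient who stays on diet.** 6 × 7 = day 42. The ± 5 day window gives days 37 to 47. As a share of the 84-day primary period: 42/84 = 50%, with 37/84 = 44% and 47/84 = 56% at the edges.

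**Step 3: what the existing contacts could give.** If all five were used, the first measurement would fall on day 7 (± 3 days, so days 4 to 10). The gaps would be 7, 14, 21, 21 and 21 days. The longest gap falls from 42 days to 21.

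**Step 4: which route records a symptom that begins and settles before week 6 in a patient who continues?**
- QLQ-C30: not scheduled in that interval.
- Informal clinic assessment: no clinic visit falls in that interval. The week 6 visit could ask about the preceding weeks, but this is not stated.
- CTCAE v4.0: a grading scale. The article does not say at which contacts symptoms are elicited to be graded.
- Record of dietary adjustments in the CRF: its stated purpose is the composition needed to reach ketosis, not symptoms.
- General adverse event reporting: applies at any time, but no standard prompt is stated.

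Only the last route clearly covers the interval.

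**The case against.** The strongest reply is that the article already handles early effects. CTCAE grading is planned, all adverse events are to be reported without a time limit, and a dietitian who changes a diet because of a symptom knows of that symptom. Patients who stop before week 6 complete the questionnaire at discontinuation, and reasons for stopping belong to the primary outcome. Habitual complaints are taken at baseline. The visit row of Table 1 includes the telephone reviews, so a clinic assessment need not exclude them, and the content of dietary review is not defined. The full protocol and CRF, not shown here, may hold the symptom questions. The outcome is descriptive, is one of many, and tolerability itself is not a progression criterion.

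Most of this stands, and it limits the point. A reader might infer that early effects are missed, that nobody is measured before week 6, or that symptoms are in fact treated at the week 1 and 3 calls. The article supports none of these as stated fact. The first conflicts with the adverse event commitment and the second with the questionnaire at discontinuation. The third is only a reasonable inference from two sections.

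The reply does not remove the point, because the article does more than leave a detail to the full protocol. It expressly chooses an informal method and prints a schedule in which ketones are reviewed at every on-diet contact after initiation while the first-named risk is not listed at the calls.

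**Conclusion.** The point holds as a weakness in how this outcome is ascertained. It is neither a contradiction nor an error of calculation. For patients who stay on diet, no structured gastrointestinal assessment is scheduled between diet start and about day 42 (37 to 47), half of the primary period. Early symptoms that settle after an adjustment depend on general adverse event reporting without a standard prompt. Ascertainment may therefore be incomplete and may differ between the two unblinded diets.

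The size of any under-recording cannot be derived from the article, and no sample size or precision figure is affected. The conclusion rests on two assumptions: that Table 1 is the complete schedule for this outcome, and that neither the week 6 questionnaire nor the week 6 visit systematically reconstructs the earlier weeks. If the full protocol or CRF already sets symptom questions at the calls, stating so would settle the point. Otherwise the change is a cheap improvement and should be made.

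**What to change.** - Replace the informal assessment with a short fixed checklist of the five symptoms given as examples in the Adverse events section: diarrhoea, constipation, nausea, reflux and abdominal discomfort.
- Grade each by the CTCAE v4.0 already planned, at every existing contact including the calls at weeks 1, 3 and 9, covering the time since the last contact.
- Record the habitual complaints already collected at baseline on the same list, so that later grades can be read against them.
- Add the row to Table 1, so that the data-completeness criterion has a denominator for this end point.
- Report each patient's worst grade to week 12, by diet, beside the QLQ-C30 results.

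The cost is a few minutes per contact and one CRF page, with a small added burden on the patient at each call. No visit or staff member is added, and no rule on diet or treatment changes.

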### Withdrawal

If there is a change in the patient’s condition that in the clinician’s opinion justifies dietary discontinuation or if the patient withdraws consent, the patient will be withdrawn from dietary treatment. In this case, data up until the point of withdrawal will be used in analysis. Unless the patient specifically withdraws consent further data will be gathered for progression-free survival and overall survival analysis.

Patients will be made aware at the point of consent that they can withdraw at any time. No reason will be required. Should a patient withdraw, data will be included in the analysis until the point of withdrawal, unless the patient states otherwise. If they wish for their data to be excluded entirely, a CRF for destruction of data will be completed.

